**The effectiveness of acupuncture in the treatment of Gulf War Illness.**

2. Phase

This is a Phase II Clinical Trial with a usual care control arm.

3. Principle Investigator/ Study Staff

PI: [name] MA MS ScD

Faculty and Co-director of Research, New England School of Acupuncture,

[name]

[contact] ext 145 [contact]

Collaborator: [name], M.Ac., Dipl.Ac

Faculty, New England School of Acupuncture,

[name]

[contact] [contact]

Collaborator: [name]

Co-director of Research, New England School of Acupuncture,

[name]

[contact] ext 140 [contact]

Medical Monitor and Screener: [name] MD

Director, Acupuncture Pain Clinic

Worcester Veterans Outpatient Clinic

Worcester, MA 01605

[contact]

Collaborator: [name] [name], PhD

Director, Neuropeptide Research Unit

Beth Israel Deaconess Medical Center

[name]

Boston, MA 02215

[contact]

4. Study Locations

The study PI is [name], MA MS ScD. She is the co-director of research at the New England School of Acupuncture, [name].

[name] MA MS ScD and [name] PhD will conduct their duties at their offices at the New England School of Acupuncture, [name]. This is also the site where [name] will conduct the medical screening. FWA00003759.

Biomarkers analysis will take place at [name] lab in the Dana Building at the Beth Israel Deaconess Medical Center, [name]. FWA00003245.

Data collection and treatments will take place at the practitioners’ offices; the study practitioners have not been hired yet. One treatment site will be the office of [name], M.Ac., Dipl.Ac.,  [name]. As a private practitioner she does not have a FWA or DUNs number. She does have a National Provider Identifier, established by the National Plan & Provider Enumeration System ([https://nppes.cms.hhs.gov](https://email.med.harvard.edu/OWA/redir.aspx?C=3ed563c61743466ab3f175942b5bb9ff&URL=https%3A%2F%2Fnppes.cms.hhs.gov)) which is [name]

5. Time Required to Complete the Study.

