We will utilize an unblinded randomized controlled trial design with a wait-list-control. A simple random sample will be used to obtain our sample from the accessible population. Volunteers will be randomly assigned to treatment or wait list arm using computer assignment.

Our primary outcome is quality of life. In an effort to better understand this disease and its treatment we are considering psychosocial variables (quality of life, depression, anxiety, mood), fatigue, sleep quality, and pain. All of the measurement instruments used in this trial have been used before and published on in peer reviewed scientific journals. All have shown good validity and reliability. Details of the measures are listed below in item “15. Study Procedures/Study Interventions**”.**

9. Study Population.

The study results will be generalizable to individuals with Gulf War Illness as determined by responses on the Gulf War Illness Symptom Checklist, who live within 90 miles of the Boston area and meet the inclusion/exclusion criteria as listed in “item 10 Inclusion/Exclusion Criteria” below. Participants will not be excluded due to age, race, ethnicity, or sex limitations.

Our study team has successfully recruited volunteers to acupuncture trials in populations with other complex diseases such as Irritable Bowel Syndrome (43), and Chronic Pelvic Pain (93), and in challenging populations such as a pediatric population (93). Based on our experience from other trials (18) we expect to screen four volunteers for every one that is enrolled.

As described in section “C. Advertisements, Posters, and Press Releases to Recruit Volunteers” we will be using two forms of recruitment; from the Gulf War Registry and by advertisement. The combination of these two techniques will promote timely recruitment and accrual.

10. Inclusion/Exclusion Criteria.

Inclusion:

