In comparison to the original CDC definition, we chose to use a broader sampling frame. The federal definition of Gulf War Illness as used for the Gulf War Registry will be used for inclusion definition (see “Gulf War Registry Description” below). Volunteers will be invited in for screening into the study if they were: 1) deployed to the “*Gulf Theater of operations, as defined by 38 CFR 3.317, includes Iraq, Kuwait, Saudi Arabia, Bahrain, Qatar, the United Arab Emirates, Oman, the Gulf of Aden, the Gulf of Oman, the Persian Gulf, the Arabian Sea, the Red Sea, and the airspace above all of these locations”* between August 1990 and the present date, 2) they have at least 2 of the following symptoms from the 3 CDC (10) clusters of symptom that have lasted for more than 6 months. Each symptom cluster must be characterized as “mild-moderate” or “severe” with at least one symptom in each cluster required to be severe. The clusters are:

A-Fatigability

- fatigue 24 hours or more after exertion

B-Mood and Cognition

- - - - feeling depressed or
      - feeling irritable or
      - difficulty thinking or concentrating or
      - feeling worried, tense, anxious or
      - problems finding words or
      - problems getting to sleep

C-Musculoskeletal

- - - - joint pain or muscle pain

Exclusion:

Volunteers will be excluded if they are

- Currently enrolled in another clinical trial
- Have another disease that likely could account for the symptoms, as determined by our Medical Monitor
- Severe psychiatric illness (in the last 2 years psychiatric hospitalization, suicidal attempt, alcohol or substance abuse, use of antipsychotic medication) as measured by the Primary Care Evaluation of Mental Disorder (Prime MD) (81).
- Unable to complete the protocol on based on the evaluation of the Medical Monitor
- Women and/or minorities are **not** excluded

Excluded volunteers will be given a list of acupuncturists in their area should they be interested in pursuing treatment on their own.

11. Description of the Recruitment Process.

Figure 5 below is a flowchart of the Recruitment and Randomization Processes planed for the study. Our initial recruitment plan is to utilize the Gulf War Illness Database to gain contact the information of potential volunteers. The process below was offered by [name] of the VA Information Resource Center in Hines, IL as the best way to gain access to these individuals. [name] e-mail is attached as a letter of support.

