B. Written Informed Consent process: At the beginning of the in-person screening visit, the Research Assistant will review each point of the Informed Consent document with the volunteer, in a private area. The Research Assistant will explain to the volunteer that it is possible that they may not be eligible for the study based on the results of the screening visit; however, if they are found to be ineligible, or change their mind about being in the study, they can be referred to acupuncturists in the community where they may be able to seek treatment on their own, should they wish. The volunteer will be encouraged to ask questions. If/when the staff member is assured that the volunteer understands the information in the Consent document, and is willing to proceed with secondary screening and potential enrollment in the study, the volunteer will be asked to sign 2 copies of the consent document, which will be co-signed and dated by the Research Assistant. One copy will be given to the volunteer, and the other will go into the volunteer’s chart. Should the volunteer be enrolled in the study, this document will be kept in a separate locked file from study data, along with other records containing the volunteers’ name or contact information.

Since this study is limited to United States veterans with Gulf War Syndrome, we do not expect volunteers to be minors, illiterate, or unable to speak or understand English.

14. Volunteer Screening Procedures.

Following the informed consent process volunteers will be given the check list of symptoms used to determine eligibility to the Gulf War Registry as described in “item 10 Inclusion/Exclusion”. Each volunteer will be screened by the study physician for general physical health status, physical and mental factors as described in the “Inclusion/Exclusion”, and asked to complete the Primary Care Evaluation of Mental Disorder (81).

15. Study Procedures/Study Interventions

Acupuncture intervention:

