Participants will receive acupuncture in private exam rooms in sessions that last about an hour. Brief interviews begin each subsequent session to review progress, prioritize symptoms, and identify any questions or concerns. After needle insertion, volunteers can expect to rest comfortably or nap. From 10 to 35 sterile, disposable needles will be inserted, with a technique characteristic of TCM known as “obtaining *de qi*,” an elicited response felt by both the patient and the acupuncturist. The needling sensation, adjusted for the comfort and safety of each patient, may be experienced as a pinch that rapidly subsides, or a sense of spreading pressure, dull ache, or warmth. Several types of needles, including from 32 to 38 gauge, and lengths from 15 mm to 50 mm, will be used on various parts of the body. Insertion depths vary by location, from subcutaneous to about 25 mm. Needles are retained 30-45 minutes. Choice of acupoints may vary during subsequent treatments to improve results.

A number of co-interventions will be used to supplement manual needling, usually 1 or 2 in each session, at the discretion of the acupuncturist. Electroacupuncture will be used for its efficacy in reducing pain and inflammation (59). Heat therapies will be used when appropriate, including heat lamp and moxibustion, a process in which a topical herbal product is heated on the needle or skin. Tui na, cupping and gua sha will be used, massage techniques in which rubbing, pressing, and scraping are applied to the body with the hands or with instruments. To prolong effects of treatment, tiny metallic balls, tacks or magnets may be applied to points after needling. The initial dose of acupuncture will be twice per week for 2 months, after which outcomes will be assessed and biological samples collected. For the following 4 months of treatment, the dose is reduced to once per week. The tapered dose of acupuncture is frequently used in clinical practice and has previously been used in research that demonstrated acupuncture efficacy for pain (9).

Volunteers in the control group will be offered 4 months of acupuncture once per week after the 2-month waiting period has elapsed. All volunteers will complete re-evaluation of outcomes instruments and biomarkers at the 6-month follow-up.

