**B. Surveys, Questionnaires, and Other Data Collection Instruments**

**(Copies of all scales are below.)**

Baseline Measurements

Screening:

- Primary Care Evaluation of Mental Disorder (Prime MD) (81)

Data Collection:

- - The Sf-36 (53)
- Multidimensional Assessment of Fatigue (85)
- The Profile of Mood States (62)
- Pittsburg Sleep Quality Index (34)
- Measure Your Medical Outcomes Profile (40)
- Beck Anxiety Inventory (63)
- McGill Pain Scale (55)
- Carroll Depression Scale (14)
- Social support, Social Networks, and Stress (56-7)
- Medication use and Expectations for Treatment
- Blood draw to examine levels of selected markers of inflammation, stress, and immune function.

Endpoint Measurements:

- - The Sf-36 (53)
- Multidimensional Assessment of Fatigue (85)
- The Profile of Mood States (62)
- Pittsburg Sleep Quality Index (34)
- Measure Your Medical Outcomes Profile (40)
- Beck Anxiety Inventory (63)
- McGill Pain Scale (55)
- Carroll Depression Scale (14)
- Social support, Social Networks, and Stress (56-7)
- Medication use and Expectations for Treatment
- Blood draw to examine levels of selected markers of inflammation, stress, and immune function.

Follow-up Measurements:

- - The Sf-36 (53)
- Multidimensional Assessment of Fatigue (85)
- The Profile of Mood States (62)
- Pittsburg Sleep Quality Index (34)
- Measure Your Medical Outcomes Profile (40)
- Beck Anxiety Inventory (63)
- McGill Pain Scale (55)
- Carroll Depression Scale (14)
- Social support, Social Networks, and Stress (56-7)
- Medication use and Expectations for Treatment
- Blood draw to examine levels of selected markers of inflammation, stress, and immune function.
- Debriefing and brief interview about study experience

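### Ongoing acupuncture is neither excluded at entry nor addressed during the 2-month wait, and the control is described in two ways, so the primary contrast can be diluted

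*Protocol*

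**What the plan says.** **Eligibility (section 10).** The only exclusion that touches concurrent treatment is "Currently enrolled in another clinical trial". The others are another disease likely to explain the symptoms, severe psychiatric illness, and "Unable to complete the protocol on based on the evaluation of the Medical Monitor". Acupuncture is not mentioned. Section 14 adds the symptom checklist, a physician's screen and the PRIME-MD, with no acupuncture rule.

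**Control arm.** Section 2 states: "This is a Phase II Clinical Trial with a usual care control arm". Section 8 states: "We will utilize an unblinded randomized controlled trial design with a wait-list-control". Section 15 describes what controls get: "Volunteers in the control group will be offered 4 months of acupuncture once per week after the 2-month waiting period has elapsed". Section 18 analyses the arm as a wait-list. No section says whether a control may have acupuncture elsewhere before the 2-month assessment.

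**Data collected.** Section 18 and part B list the instruments for baseline, endpoint and follow-up. The one item on concurrent treatment is "Medication use and Expectations for Treatment". Acupuncture obtained outside the study is not named.

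**Primary comparison.** Section 18 compares SF-36 Physical Component Summary improvement between the arms at 2 months by t-test at alpha 0.05. Section 12 sizes the trial for a 7-point difference with SD 20 and 60 per group.

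**The concern.** The trial compares volunteers given study acupuncture with volunteers waiting for it. That comparison needs the waiting arm to be largely free of acupuncture for 2 months, or an explicit decision that it need not be. The protocol gives neither. Read literally, a veteran with a standing acupuncture appointment meets section 10. If allocated to wait, that veteran may carry on. If allocated to treatment, study acupuncture adds to or replaces what was already being received. In both cases the person adds little to the difference being tested.

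The two control labels make this harder to settle. A usual-care arm may include whatever a veteran ordinarily uses, acupuncture among it. A wait-list arm is normally meant to isolate the effect of starting the intervention. Staff handling a query from a control could reasonably answer either way.

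Outside use is plausible, though not quantified. Section 6 says acupuncture is commonly used for many symptoms of this illness and mentions a pilot project offering it to veterans. Recruitment text in part C offers free acupuncture, which will attract people interested in it. The trial is unblinded, so controls know they are waiting.

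At stake is the power of the primary test. Section 18 also plans to read the wait-list change from 2 to 6 months as information on weekly treatment. Acupuncture during the wait would blur that starting point too.

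**Working it through.** **1. The plan's own figure.** Inputs from section 12: difference 7, SD 20, n = 60 per group. Alpha 0.05 is from section 18; two-sided is my assumption, as the protocol does not say.

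- Standard error = 20 × √(2/60) = 3.65.
- Power = Φ(7/3.65 − 1.96) = Φ(−0.04) = 48%.

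The stated 80% does not reproduce; one-sided testing gives 61%. An 80% figure would need an SD of about 13.7. That is a separate matter and the present point does not depend on it, so both versions are carried below.

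**2. Dilution from concurrent acupuncture.** Two routes lead to one formula.

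- Ongoing users: a share g has acupuncture whichever arm they are in and contributes zero contrast. Expected difference = (1 − g) × 7 + g × 0 = 7(1 − g).
- Controls who start outside acupuncture during the wait: if a share g of controls gains the full 7 points, the difference is 7 − 7g = 7(1 − g).

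The documents give no g, so the values are illustrative. Required sample size rises by 1/(1 − g)².

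| g | Difference | Standardised (SD 20) | Power, SD 20 | Power if the stated 80% is accepted | Sample-size factor |
|---|---|---|---|---|---|
| 0 | 7.0 | 0.35 | 48% | 80% | 1.00 |
| 10% | 6.3 | 0.315 | 41% | 71% | 1.23 |
| 20% | 5.6 | 0.28 | 34% | 61% | 1.56 |
| 30% | 4.9 | 0.245 | 27% | 50% | 2.04 |

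This is an upper bound for a given g. Study treatment is twice weekly for the first 2 months with co-interventions (section 15), so it may still add something for a person already having lighter outside treatment.

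**3. Past acupuncture.** Let b be residual benefit at baseline, the same in expectation in both arms after randomisation. Let ρ be the fraction of it still present in controls at 2 months. Suppose study treatment brings people to a benefit of 7.

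- Change in the treatment arm: 7 − b.
- Change in controls: ρb − b.
- Difference: (7 − b) − (ρb − b) = 7 − ρb.

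The raised baseline cancels. The contrast shrinks only if ρ is above zero, meaning the effect persists through the 2 months. The other route is a ceiling that limits further improvement. Section 10 requires severe symptoms at entry, which makes a ceiling less likely.

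**4. Direction.** Randomisation balances ongoing use between arms in expectation, and acupuncture among controls improves controls. The bias is towards no difference, so the false-positive rate is not inflated.

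**The case against.** The best defence is that study acupuncture against a wait with ordinary care is a legitimate pragmatic comparison, and that a wait-list arm keeping its ordinary care fits both labels. Section 7 asks about effectiveness in treating the illness and does not specify a comparison with no acupuncture at all. The usual-care label appears once, while the operative sections consistently describe a wait-list. Free acupuncture after only 2 months is a reason for controls to wait, and section 12 expects veterans to have fewer other options for care. All of this stands as a reason to expect modest outside use. It does not tell staff whether to enrol a current user or what to tell a waiting control. A deliberately pragmatic design would still need to say so and to record the exposure.

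Stronger readings are tempting and the documents do not support them:

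- A reader might infer that any earlier acupuncture biases the result towards zero. A raised baseline shared by both arms does not do this by itself.
- A reader might take the consent discussion's offer that "they can be referred to acupuncturists in the community where they may be able to seek treatment on their own" as evidence of contamination. It concerns people found ineligible or who change their mind before randomisation. The lists in sections 10 and 24 go to excluded volunteers and to those whose participation has ended. None is directed at waiting controls.
- A reader might point to the screening physician's post as "Director, Acupuncture Pain Clinic". Recruitment is by registry letter and advertisement, and no section names that clinic as a source.
- A reader might conclude that outside use could never be examined afterwards. The health history and intake forms in section 15, the telephone screener and the medication form are not shown. One can say only that no listed item names outside acupuncture.

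**Conclusion.** The point holds for concurrent acupuncture, at entry and during the wait. Section 10 admits current users, nothing addresses outside acupuncture before the 2-month assessment, and the control is described in two ways that would give different answers. Eligibility and control-arm conduct belong in the protocol, so this is not something left to a statistical analysis plan.

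The consequence is a conservative loss of contrast and power. Its size cannot be derived from the documents. Under the assumption that affected volunteers add no contrast, 10% to 30% of them would take 7 points down to between 6.3 and 4.9. Past acupuncture is a secondary issue that depends on persistence or a ceiling. The matter is worth settling before enrolment because it is cheap then and hard to repair later; it does not invalidate the design.

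**What to change.** 1. In section 10, add an exclusion for volunteers currently having acupuncture, asked at telephone screening. Whether to add a look-back period, and how long, is for the sponsor to set before enrolment.
2. Reconcile section 2 with sections 8, 15 and 18 so the control has one description. State whether acupuncture outside the study is allowed before the 2-month assessment, and say so in the consent discussion.
3. Add an item on acupuncture obtained outside the study to the existing medication-use form, in both arms, at baseline, 2 and 6 months.

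The cost is one eligibility line, one consent sentence, one form item and a slightly smaller eligible pool. On section 9's expectation of four screened per enrolled volunteer, 134 volunteers need 4 × 134 = 536 screens. If 10% of otherwise eligible people were current users, that would become 536/0.9, about 596. This factor of 1/(1 − g) falls on screening. If the same people were enrolled and contributed no contrast, the factor would be 1/(1 − g)² on the randomised sample.

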***Overview***

*The Gulf War Registry (GWR) is a dataset of veterans who have participated in the Persian Gulf War, Operation Iraqi Freedom and had a GWR examination at a Department of Veterans Affairs (VA) medical facility. This centralized registry is maintained to enable VA to keep veterans informed on research findings or new compensation policies through periodic newsletters. It provides a mechanism to catalogue prominent symptoms, reproductive health, reported exposures and diagnoses, and to communicate with GW veterans. The voluntary, self-selected nature of the registry makes it valuable for health surveillance; however, it is not designed or intended to be a research tool and therefore, the results cannot be generalized to represent all GW veterans’ illnesses. The Gulf War period of conflict is between August 2, 1990, and a yet to be determined official termination date and Operation Iraqi Freedom began on March 19, 2003 through the present date. The Gulf Theater of operations, as defined by 38 CFR 3.317, includes Iraq, Kuwait, Saudi Arabia, Bahrain, Qatar, the United Arab Emirates, Oman, the Gulf of Aden, the Gulf of Oman, the Persian Gulf, the Arabian Sea, the Red Sea, and the airspace above all of these locations. The GWR is centrally housed and maintained at the CFD. Registry data is entered via Environmental Agents Service Web site into the registry database for incorporation into the registry master file. Processing occurs nightly. The primary users are the Office of Public Health and Environmental Hazards, Environmental Agents Service, and Environmental Epidemiology Service.*

***Features***

*Provides a registry for GW veterans who have had a GWR examination at a VA medical*

*facility. Provides a method to communicate with GW veterans through periodic newsletters. Provides information that may assist in generating hypotheses for future research studies. Provides on-line menu for editing and simple look-up to Austin Corporate Franchise Datacenter by the VA Central Office. Provides Veterans Health Administration (VHA) with the capability to track patient demographics, symptoms, reproductive health, reported exposures and diagnoses. Provides report generation capability* (89).

We will select volunteers from the database to be contacted using an IRB approved opt-out letter (see section “C. Advertisements, Posters, and Press Releases to Recruit Volunteers”).Because the demographics of GWI veterans are unpublished, there may be an insufficient population of GWI veterans in the Boston area. However, we will consider adding treatment sites if GWI veterans are found to be clustered in greater numbers in other parts of the New England area. One of our first study tasks upon gaining access to the GWI registry is to determine where the GWI veterans reside and what their level of interest is. This will include mailing our IRB approved recruitment letter to a sample of 100 GWI veterans in the greater Boston area, in order to gauge interest. A no-duplicates random number generator will be used to choose the names for each mailing. If we appear to have sufficient numbers the response rate can then be used to manage study flow and determine the frequency of recruitment mailings.

If recruitment using the Gulf War Registry proves insufficient after 3 months of attempts, we will utilize the advertisements material listed in section “C. Advertisements, Posters, and Press Releases to Recruit Volunteers”, which including announcements in the Boston area newspapers, and VA newsletters.

No published estimates of GWI prevalence for our catchment area are available, but we are confident that we will be able to reach our recruitment target of 120 as: 1) peer-reviewed estimates of GWI prevalence are approximately 200,000 veterans nationally (33), 2) our budget allows us to add additional treatment sites if necessary, 3) our use of multiple recruitment methods will allow us to access interested volunteers.

**Figure 5. Recruitment/Randomization Flowchart: The** **effectiveness of acupuncture in the treatment of Gulf War Illness.**

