**GWI Registry**

**“Opt Out” letter**

**Opted Out (refused)**

**Advertisements**

**Initial Screening**

**(Telephone)**

**INELIGIBLE**

**Medical Screening**

**INELIGIBLE**

**Eligible Volunteers**

**Treatment**

**Waitlist**

**Follow-up**

**Follow-up**

**`**

12. Sample Size Justification.

Our study is designed to give us adequate power to detect clinically meaningful differences between treatment groups. Previous acupuncture research using our main outcome, the SF-36, in pain conditions (41,52) show a consistent standard deviation of 20 points in the Physical Component Summary score of the SF-36 for both baseline values and change scores. Sixty individuals per group (total n=120) would offer us a power of 80% to detect the difference between groups of 7 points. Using Cohen’s d estimation of effect size (20):

[figure not shown]

A sample size of 60 will allow us to see a moderate effect. In further support of our main outcome a 7 unit improvement has been shown to be clinically relevant (97,55,78).

Although we do not expect attrition to be large, we expect a dropout rate of no more than 10% by the 8 week endpoint. This trial is longitudinal which could increase drop-out rate. Still a veteran’s population will be less mobile and may have fewer other options for care; both of these factors should increase adherence. We will thus oversample to a target sample size of 67 volunteers per group to assure that our power to detect effects is maintained. The resulting overall sample will be 134 (one treatment group and one wait list group).

13. Description of Informed Consent Process.

The informed consent process will occur in two stages. Verbal informed consent will be administered prior to the initial telephone screening, and written informed consent will be administered in person, at the start of the screening visit.

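### The recruitment target of 120 in section 11 is the pre-dropout number; section 12 requires 134 to be enrolled

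*Protocol*

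**What the plan says.** The protocol gives two totals for the number of volunteers to bring into the trial.

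- **Section 11 (Description of the Recruitment Process)**, after the account of the Gulf War Registry: "we are confident that we will be able to reach our recruitment target of 120". Three supporting reasons follow: the national prevalence of the illness, a budget that permits more treatment sites, and the use of several recruitment methods.
- **Section 12 (Sample Size Justification)** starts from the same total in a different role: "Sixty individuals per group (total n=120) would offer us a power of 80% to detect the difference between groups of 7 points". It then says "we expect a dropout rate of no more than 10% by the 8 week endpoint" and draws the consequence: "We will thus oversample to a target sample size of 67 volunteers per group to assure that our power to detect effects is maintained". The total is explicit: "The resulting overall sample will be 134 (one treatment group and one wait list group").

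Section 8 (Study Design) describes two randomised arms, and the equal group sizes in section 12 imply 1:1 allocation. Section 9 (Study Population) expects four volunteers screened for each one enrolled. Nothing elsewhere in the protocol reconciles 120 with 134.

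**The concern.** Both sections speak of a target, and the targets differ by 14 volunteers. In section 12, 120 is the number that must remain for the primary comparison at 2 months. In section 11 the same number is what is to be recruited, and recruitment comes before dropout. The two agree only if nobody drops out, and section 12 explicitly declines to rely on that.

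What is at stake is the dropout allowance. Section 12 adds seven volunteers per group for one stated reason, to keep power at its planned level. A trial recruited to the section 11 figure has no such allowance. Section 11 is also the operational part of the protocol, covering mailings, the three-month point at which advertisements are added, and possible extra sites. A wrong total there is more than a matter of wording.

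**Working it through.** **Inputs.** Needed per group before dropout: 60 (section 12). Dropout: at most 10% by week 8 (section 12). Enrolment per group: 67, total 134 (section 12). Recruitment target: 120 (section 11). Difference: 7 points; SD: 20 points (section 12). Test: Student's t-test at alpha 0.05 (section 18, Data Analysis). The number of sides is not stated, so two-sided is assumed.

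**1. Reproduce the protocol's enrolment figure.** Enrolment per group = n / (1 − dropout) = 60 / 0.9 = 66.7, rounded up to 67. Total = 2 × 67 = 134. This matches section 12 exactly. As a check, 67 × 0.9 = 60.3 per arm remain.

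**2. Recruit to section 11 instead.** 120 recruited is 60 per arm. At 10% dropout, 60 × 0.9 = 54 per arm remain, 108 in total. At zero dropout, 60 per arm remain. The range is therefore 54 to 60 per arm, and the enrolment shortfall is 134 − 120 = 14.

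**3. Power on the protocol's own premise.** If 60 per arm gives 80% power (normal approximation, two-sided 0.05), the standardised difference at n = 60 is 1.960 + 0.842 = 2.802. It scales with √n, so at 54 it is 2.802 × √(54/60) = 2.658. Power = Φ(2.658 − 1.960) = Φ(0.698) ≈ 75.7%. At the full 10% dropout the loss is from 80% to about 76%.

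**4. Power from the stated inputs, kept separate.** Power ≈ Φ[(7/20) × √(n/2) − 1.960].

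| Per arm | (7/20) × √(n/2) | Power |
|---|---|---|
| 54 | 1.819 | 44.4% |
| 60 | 1.917 | 48.3% |
| 67 | 2.026 | 52.6% |

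The t distribution gives 43.7%, 47.7% and 52.0%. The 80% at 60 per group does not follow from a 7-point difference and an SD of 20. On these inputs, going from 60 to 54 per arm costs about 4 percentage points. The gap between 48% and 80% has nothing to do with the recruitment target.

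**5. Screening implied by the 4:1 ratio.** 4 × 134 = 536, against 4 × 120 = 480. Neither product appears in the protocol.

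**The case against.** The best defence is that section 12 governs. It is the sample-size section, it states 134 and gives its reason, and a reader can see that 120 is its pre-inflation total. The figure in section 11 sits in a sentence about feasibility and is not a rule for stopping enrolment. A number left unadjusted is the likely explanation. That is fair as to cause. But the protocol gives neither section precedence, and section 11 calls 120 the recruitment target, so the text is still wrong as it stands. Reading 120 as completers does not fit either: the sentence is about reaching volunteers and does not mention dropout.

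A reader might also infer several stronger points, which the protocol does not support:

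- **That 54 per arm is certain.** The 10% is an upper limit, so the outcome is 54 to 60 per arm.
- **That mailing or screening is planned too low.** No volume is derived from 120. Section 11 begins with a sample mailing of 100 letters and lets the response rate set the frequency of later ones.
- **That the feasibility argument depends on 120.** None of its three reasons is quantified against a total, and each reads the same with 134.
- **That power near 44% results from this discrepancy.** Most of that shortfall comes from the 80% claim itself, a separate defect.

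**Conclusion.** The contradiction holds. Section 11 gives as its recruitment target a number that section 12 treats as the requirement before dropout, and section 12's enrolment figure of 134 reproduces exactly. The effect is moderate: 14 too few enrolled, 54 to 60 per arm at 2 months, and power of about 76% in place of 80% at the full 10% dropout.

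The 76% rests on accepting the protocol's premise of 80% at 60 per arm, on 1:1 allocation, and on a two-sided test. It would be wrong to conclude that enrolling 134 secures 80% power: on the stated difference and SD, even 67 analysed per arm gives only about 53%.

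**What to change.** In section 11, change the recruitment target to 134 randomised (67 per arm), and mention 120 only as the minimum expected number with 2-month data. If a screening figure is wanted there, the section 9 ratio implies about 536 screened, to be labelled as derived.

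This is a one-line correction that leaves section 12's stated sample size unchanged. The basis for 80% power needs its own correction; if that changes the sample size, section 11 should be updated at the same time so that both sections show one enrolment figure.
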